## Abstract

**Background:**

Frail older adults have reduced functional and physiological reserves, rendering them more vulnerable to the effects of hospitalization, which frequently results in failure to recover from the pre-hospitalization functional loss, new disability or even continued functional decline. Alternative care models with an emphasis on multidisciplinary and continuing care units are currently being developed. Their main objective, other than the recovery of the condition that caused admission, is the prevention of functional decline. Many studies on functional decline have discussed the available evidence regarding the effectiveness of acute geriatric units. Despite the theoretical support for the idea that mobility improvement in the hospitalized patient carries multiple benefits, this idea has not been fully translated into clinical practice.

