### Statistics and sample size

The required simple size to detect a difference of 15 % in the frequency of patients that get at discharge a functional improvement greater than 10 points in Barthel Index is 161 patients in each group. Assuming a loss of 15 % of patients in the follow-up, we fixed a final sample size of 185 patients per group.

In an initial descriptive analysis, for qualitative variables we will calculate frequencies and confidence intervals, and for continuous variables, statistics of central tendency and dispersion such as means, standard error and confidence intervals or median and interquartile range. In order to assess the extent of the therapeutic effect, we will compute for every patient the difference between final and initial level of the outcome variables. Normality of continuous variables will be checked graphically and through K-M and Shapiro-Wilk tests, and their differences between groups by means of parametric tests (T-Tests, ANOVA) or non-parametric tests (Mann–Whitney U, Kruskal- Wallis). A Bonferroni post-hoc test will be used to evaluate statically significant (*p* < 0.05) group and time differences. Associations between clinical and biomechanical tests will be reported by their correlation coefficient (r value), level of significance (p value), and the amount of variance explained (r2 value). Values of r will be used to indicate small (r = 0.10), medium (r = 0.30), and large (r = 0.50) size correlations (i.e., effect size). Finally, the relationship between qualitative variables will be assessed through χ^2^ and Fisher exact tests. The level of statistical significance will be 0.05. Data will be analyzed with SPSS package 21.0

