### Outcome measures

#### Primary outcome

The primary outcome measure is the change in functional and cognitive status during the study period. The functional capacity of patients will be evaluated by the Short Physical Performance Battery (SPPB) [47], which evaluates, balance, gait ability, and leg strength using a single tool. The total score will range from 0 (worst) to 12 points (best). The SSPB test has been shown to be a valid instrument for screening frailty and predicting disability, institutionalization, and mortality. A total score of less than 10 indicates frailty and a high risk of disability and falls. One-point change in the score has clinical relevance [48, 49]. Loss of handgrip of the dominant hand is a useful tool for the measurement of functional capacity. It is a strong predictor of disability, morbidity, and mortality as well as one of the components of Fried’s frail phenotype. Furthermore, the functional status of patients will also be assessed before measurements with the Barthel Index, an international and validated tool of disability. The scores range from 0 (severe functional dependence) to 100 (functional independence) [50]. Gait ability will be assessed using the 6-metre gait velocity test (GVT). Starting and ending limits will be marked on the floor with tapelines for a total distance of 8 m. Participants will be instructed to walk in their self-selected usual pace for two attempts. The results of both trials will be averaged to obtain a single value. The first and last metre, considered the warm-up and the deceleration phases, respectively, will not be included in the calculations of the gait assessment. Dual task conditions (gait evaluation during the simultaneous performance of a cognitive motor action) have recently been recognized as a sensitive assessment method for interactions between cognition, gait, falls and frailty. Changes of gait parameters (i.e., gait velocity and gait variability) while performing a dual task test (dual task cost) could be early predictors of falls risk (50) and useful tools for functional evaluations in frail elderly patients. Exercise can modify dual task cost and consequently fall risk and functional capacity (31). The dual-task paradigm [51] will be used in the 6-m habitual gait velocity test (GVT). Two trials will be performed to assess the gait velocity while performing a verbal or counting task (verbal GVT and counting GVT, respectively). During the verbal dual-task condition (verbal GVT), we will measure the gait velocity while participants are naming animals aloud. During the arithmetic dual-task condition (counting GVT), we will assess the gait velocity while participants are counting backward aloud from 100 by ones. The cognitive score will be measured by counting the number of animals named (dual-task with verbal performance) or determining how many numbers were counted backward (dual-task with arithmetic performance). Isometric upper (right hand grip) and lower limb (right knee extensors and hip flexors) muscle strength will be measured using a manual dynamometer. Maximal dynamic strength will be assessed using the 1RM test in the bilateral leg press, knee extension and bench press exercises using exercise machines (Exercycle, S.L., BH Group, Vitoria, Spain). In the first assessment, the subjects will warm up with specific movements for the exercise test. Each subject's maximal load will be determined in no more than five attempts, with a 3-min recovery period between attempts. After determination of the 1RM values, the subjects will perform ten repetitions at maximal velocity at intensities of 50 % of 1RM to determine the maximum power (w) and the loss of power during the ten repetitions in the leg press machine. The power will be recorded by connecting a velocity transducer to the weight plates (T-Force System, Ergotech, Murcia, Spain). During all neuromuscular performance tests, a strong verbal encouragement will be given to each subject to motivate them to perform each test action as optimally and rapidly as possible. Qualified fitness specialists will individually monitor and carefully supervise all training sessions and provide instruction and encouragement during all sessions. Distribution of the training sessions throughout the day should minimize cumulative fatigue and help to maintain adherence. Adherence to the exercise intervention programme will be documented in a daily register of sessions. Changes in cognitive-affective status after the intervention will be measured using the Mini Mental State Examination, Yesavage GDS and Trail Making Test (Table 3).

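### The Barthel criterion used to size the trial cannot be met from a baseline of 90 or more and does not separate stability from decline; a baseline-adjusted comparison of discharge Barthel would mend this with data already collected

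*Protocol article*

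**What the plan says.** All references are to the protocol article.

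- **Sizing (Statistics and sample size).** The trial is powered to "detect a difference of 15 % in the frequency of patients" who show, at discharge, a "functional improvement greater than 10 points in Barthel Index". The number required "is 161 patients in each group". With the next step, "Assuming a loss of 15 % of patients in the follow-up", this becomes the recruitment target: "we fixed a final sample size of 185 patients per group".
- **Scale (Primary outcome).** For the Barthel Index, "The scores range from 0 (severe functional dependence) to 100 (functional independence").
- **Entry (Study participants and eligibility criteria).** A Barthel of at least 60 is required. No upper limit is set, and the text does not say whether the score is pre-admission or at the baseline visit.
- **Analysis (Statistics and sample size).** For each outcome variable, a final-minus-initial difference is computed per patient. The groups are compared by t-test or ANOVA, or by Mann–Whitney or Kruskal–Wallis. No adjustment for the baseline value is described.
- **Primary outcome.** This is the change in functional and cognitive status, covering the SPPB, the Barthel and other measures. The gain of more than 10 points appears only in the sizing sentence.
- **Timing (Table 1).** Barthel is collected at T1 (baseline), T2 (after the training or control period), T3 and T4.

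**The concern.** The scale, the entry rule and the responder definition do not fit together. A strict gain above 10 on a scale capped at 100 needs a starting score below 90, yet patients at 90 or above may enter. They count in the denominator of both groups and can never count in the numerator, so they carry no information on the criterion that justifies the sample size. The criterion also gives one code to a patient who keeps function and to one who loses 30 points.

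At stake is how demanding the 15-point target really is. Any difference must come entirely from patients with room to gain, and the protocol does not say how many there are. If the dichotomy were also used to report efficacy, it would discard the part of the Barthel change that lies below zero.

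**Working it through.** **1. The plan's own figure.** Inputs from the text: a 15-point difference (read as absolute), 161 per group, and significance level 0.05. Assumed, because not given: a two-sided test, the power and the control rate. The pooled two-proportion formula is

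n = [1.96·√(2p̄(1 − p̄)) + z_power·√(p₁(1 − p₁) + p₂(1 − p₂))]² / (p₂ − p₁)².

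- 29 % v 44 % at 80 % power: p̄ = 0.365, n = 160.5, that is 161.
- 30 % v 45 % at 80 % power: 163.
- 15 % v 30 % at 90 % power: 161.

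So 161 is attainable under ordinary assumptions, although the unstated inputs cannot be pinned down. The final figure matches 161 × 1.15 = 185.15.

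**2. The ceiling.** Maximum gain = 100 − T1 score.

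| T1 Barthel | 60 | 70 | 80 | 85 | 90 | 95 | 100 |
|---|---|---|---|---|---|---|---|
| Maximum gain | 40 | 30 | 20 | 15 | 10 | 5 | 0 |
| Gain above 10 possible? | yes | yes | yes | yes | no | no | no |

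This takes T1 as the starting point, in line with the final-minus-initial rule in the statistics section.

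**3. What 15 points overall requires of the others.** Let f be the share with T1 Barthel of 90 or more. It is not given, so 10 to 50 % is assumed. Ceiling patients contribute zero in both groups, so overall difference = (1 − f) × difference among the rest, and the latter must be 15/(1 − f).

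| f | 10 % | 20 % | 30 % | 40 % | 50 % |
|---|---|---|---|---|---|
| Points needed among the rest | 16.7 | 18.8 | 21.4 | 25 | 30 |

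**4. Sensitivity range only.** Suppose instead that the 15 points (30 % v 45 %, assumed) hold only among patients able to respond. The overall rates are then 0.30(1 − f) v 0.45(1 − f), and power at 161 per group, two-sided 0.05, is:

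| f | 0 | 10 % | 20 % | 30 % | 40 % | 50 % |
|---|---|---|---|---|---|---|
| Overall difference (points) | 15 | 13.5 | 12 | 10.5 | 9 | 7.5 |
| Power | 79.7 % | 72.8 % | 65.3 % | 57.2 % | 48.9 % | 40.6 % |

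Under the same assumptions, leaving out the ceiling patients gives 161 × 0.7 ≈ 112 per group and 64 % power at f = 30 %, and 161 × 0.5 ≈ 80 per group and 50 % power at f = 50 %. The restricted denominator is smaller but loses no information, so its power is higher than the 57 % and 41 % in the table.

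**5. Change score v baseline adjustment.** With equal variance σ² at both visits and correlation ρ, the comparison of change scores has variance proportional to 2σ²(1 − ρ), and the baseline-adjusted comparison to σ²(1 − ρ²). The ratio is (1 + ρ)/2, which is never above 1. For an assumed ρ of 0.3, 0.5 or 0.8 it is 0.65, 0.75 or 0.90.

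**The case against.** The case on the other side is substantial, and most of it stands.

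- **The criterion is not the named outcome.** It occurs once, in the sizing sentence. The planned per-patient differences are signed, so they tell a 30-point loss from no change. A reader might infer that benefit through avoided decline would go unseen in this trial. The documents do not support that: it is true of the sizing dichotomy alone.
- **Preventing decline is not stated as the trial's aim.** A reader might take it so from the abstract's Background, where the main objective "is the prevention of functional decline". The subject of that sentence is alternative care models. The hypothesis in the Discussion concerns improving functional capacity, which a gain-based criterion fits, although the Discussion also expects less impairment after hospitalization.
- **The plain reading leaves 161 untouched.** The 15 % is a difference among patients, without restriction to those below 90, so ceiling patients are already inside both groups' rates. The power losses in step 4 arise only if the 15 points are moved to a subgroup that the protocol does not name.
- **The ceiling share may be small.** If the entry score is pre-admission, T1 scores may be lower. The Background cites an earlier study from the department with impairment on admission in 80 % of susceptible patients.

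One objection does not hold: that a rate restricted to patients below 90 would cost power. Step 4 shows the opposite under the same assumptions.

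What remains is the exact ceiling, the lumping of stability with loss in the sizing criterion, and a planned change analysis with no baseline adjustment. That analysis records decline, but the top of the scale still compresses gains in it.

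**Conclusion.** The point holds as a limited one about the design of the measure. That no patient with T1 Barthel of 90 or more can be a responder follows exactly from the scale, the entry rule and the strict threshold, and needs no assumption beyond T1 as the starting point. The criterion also treats no change and decline as the same result.

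The size of the consequence is unknown, because the document gives no Barthel distribution. If 15 points is meant for all entrants, the sample size stands and the implied target among patients able to respond is 16.7 to 30 points for f between 10 and 50 %. The fall in power from about 80 % to between 73 and 41 % is a sensitivity range that rests on an assumed f, assumed rates of 30 % v 45 % and a different reading of the 15 %. It is not evidence that the trial is underpowered.

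**What to change.** 1. In Statistics and sample size, state that Barthel at discharge (T2) will be compared between groups in a model adjusted for T1 Barthel: ANCOVA, or an ordinal equivalent if the scores are too skewed or bunched at the top. Gain and loss then both count, and in large samples the comparison is at least as precise as the unadjusted change score. It does not abolish the ceiling, but it compares patients at like baseline.
2. If a responder rate is reported, show improved, unchanged and declined with their cut-offs. Add the rate of gains above 10 points among patients with T1 Barthel below 90 as a supplementary summary, with its smaller denominator stated.
3. Beside the sizing sentence, say that the 15 points apply to all randomized patients, if that is what was meant, and give the assumed share at 90 or above.

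The cost is wording only. Barthel is already collected at T1 and T2, and neither the visit schedule nor the recruitment target changes. Recruitment was already open when the article was written, so the change should be dated and made before any comparison by group. The supplementary rate will have a wider interval than its full-sample label suggests, which is why its denominator must be shown.

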## Trial status

The trial commenced recruitment on March 5, 2015 and is currently open for recruitment. Recruitment will cease when 370 participants have been randomized. It is anticipated this target will be reached by March 2017.

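### With the stated 15% loss, 185 per group leaves about 157 patients, 4 short of the required 161; 185 covers a loss of at most 13%

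*Protocol article*

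**What the plan says.** The sizing is set out in two sentences of the protocol article, under Statistics and sample size. The trial is sized "to detect a difference of 15 % in the frequency of patients that get at discharge a functional improvement greater than 10 points" on the Barthel Index, and the number needed for this "is 161 patients in each group". The next sentence makes the allowance for attrition: "Assuming a loss of 15 % of patients in the follow-up", and then "we fixed a final sample size of 185 patients per group". The same section gives the test level: "The level of statistical significance will be 0.05".

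Under Trial status, the article carries the result into the conduct of the trial: "Recruitment will cease when 370 participants have been randomized". That is 2 × 185, so no further margin is added there.

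**The concern.** An allowance for loss should leave the required number of patients once the assumed loss has occurred. Here it does not. If 370 patients are randomised and exactly 15% are lost, the trial has gone as planned and still ends below its own requirement of 161 per group.

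At stake is the consistency of the sample-size statement, which readers will use to judge whether the trial reached its target. All three figures stand in the article, so this is a disagreement between stated numbers and not a detail left to a fuller document. No further document could make 85% of 185 equal to 161.

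**Working it through.** **Inputs**, all from the protocol article:
- required number per group, n = 161 (Statistics and sample size)
- assumed loss, d = 15% (same section)
- final size per group, N = 185 (same section)
- total randomised, 370 = 2 × 185 (Trial status)
- significance level 0.05 (Statistics and sample size); taken as two-sided for the power check only, which is my assumption

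**Reproducing the plan's figure.** The form n × (1 + d) gives 161 × 1.15 = 185.15, which rounds to 185. The match is close, but the article shows no formula, so the mechanism is inferred.

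**What 185 leaves.** N × (1 − d) = 185 × 0.85 = 157.25, or about 157 per group. The shortfall is 161 − 157 = 4 per group.

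**What a 15% loss requires.** n / (1 − d) = 161 / 0.85 = 189.4, rounded up to 190 per group, or 380 in total. That is 5 more per group and 10 more in total than stated.

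**What loss 185 covers.** 1 − n/N = 1 − 161/185 = 13.0%. Put differently, the 24 patients added are 14.9% of 161 but only 13.0% of the 185 randomised.

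**Effect on power.** The article states no planned power, so I take two usual values as assumptions. If 161 per group gives power P, the power at 157.25 is approximately Φ[(z₀.₉₇₅ + z_P) × √(157.25/161) − z₀.₉₇₅], with √(157.25/161) = 0.988.
- P = 80%: (1.960 + 0.842) × 0.988 − 1.960 ≈ 0.81, so power is about 79.1%.
- P = 90%: (1.960 + 1.282) × 0.988 − 1.960 ≈ 1.24, so power is about 89.3%.

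A direct comparison of two proportions (pooled normal approximation, two-sided 5%) agrees. Going from 161 to 157 per group lowers power from 90.0% to 89.3% for 15% versus 30%, and from 79.7% to 78.7% for 30% versus 45%. These rates are illustrations and are not in the article. The loss is 0.7 to 1.0 percentage points.

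**The case against.** Two objections carry weight.

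*The effect is too small to matter.* The gap between 185 and 190 is 2.7% of the stated size, and the power cost is about 1 point. This stands as a statement about size: no design feature or analysis has to change. It does not make the three figures agree.

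*The loss may not apply to the sizing endpoint.* The trial is sized on Barthel improvement at discharge, while the 15% is described as a loss during follow-up. Study design and setting places further visits at one and three months after discharge. If the 15% refers to those visits, fewer patients would be missing at discharge, and 185 is enough up to 13.0%. The article does not settle which is meant. The figure of 157 is therefore conditional for the discharge endpoint. The sentence still needs correcting, because it applies the 15% to this very calculation.

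A reader might also infer more than the article supports:
- *That the trial is seriously underpowered.* A drop of about 1 point does not show this.
- *That the unstated control rate and power are a further defect.* A journal article may leave such inputs to the full protocol, and this one claims no power that could be contradicted. The figure of 161 also does not identify the inputs. With the pooled formula and two-sided 5%, it results from 29% versus 44% or 56% versus 71% at 80% power, and from 15% versus 30% or 70% versus 85% at 90% power.
- *That power falls to 76–77%.* Those values appear at 157 per group if a control rate of 45–50% is assumed. The same rates give 77–78% at the full 161, so only about 1 point comes from the attrition allowance.

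**Conclusion.** The point holds as a small arithmetic error: the stated size misses the stated target under the stated loss. The shortfall is about 4 patients per group after loss, or 5 per group before it, and the cost is about 1 percentage point of power.

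The mismatch rests only on the article's own 161, 15% and 185. The power figure also rests on a two-sided 5% test and a planned power of 80% to 90%. Its relevance to the discharge endpoint depends on the 15% loss applying at discharge. That the allowance was made by multiplying by 1.15 is likely but not documented, and the conclusion does not need it.

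**What to change.** Keep 370 and replace the attrition sentence under Statistics and sample size with wording such as:

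> 185 per group leaves the required 161 if loss is at most 13%; with 15% loss about 157 per group remain, with power about 1 percentage point below that planned at 161.

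The cost is one sentence and a slightly less favourable stated figure. No extra patients are needed, and the recruitment target under Trial status can stay as it is.

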## Study design and setting

This study is a randomized clinical trial conducted in the Department of Geriatrics of a tertiary public hospital with 35 beds allocated. Hospitalized patients who meet the inclusion criteria will be randomly assigned to the intervention or control group. Patient recruitment will begin within the first 48 h of admission to the ward, and these patients will be identified through a list of patients admitted to the hospital and assigned to the Department of Geriatrics. The study flow diagram is shown in Fig. 1. After signing an informed consent form, the subjects will be randomly assigned (as explained below) to either the intervention or control group. The researcher who decides whether the patient is assigned to the intervention or control group will not be the attending physician. Patients or their relatives (if the patient has cognitive impairment) will be informed of the random inclusion in one group, but will not be informed as to which they belong. The data for both the intervention group and the control group will be obtained at four different times: the initial visit during the acute hospitalization, at discharge, and at one and three months after discharge from the outpatient clinic. Time of measurement of the different variables is shown in Table 1. The protocol employs relevant standard protocol items for clinical trials according to the SPIRIT 2013 statement [44] and follows the CONSORT statement [45] for transparent reporting. The trial is registered at ClinicalTrials.gov, identifier NCT02300896.

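### Continuous outcomes are compared as raw change scores without baseline adjustment, and a normality check chooses between a mean comparison and a rank test: valid, but less precise and less interpretable than it need be.

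*Protocol article*

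**What the plan says.** All of the analysis text is in the Statistics and sample size section of the protocol article.

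- **Effect measure.** To gauge the therapeutic effect, "we will compute for every patient the difference between final and initial level of the outcome variables". No baseline covariate is named.
- **Choice of test.** "Normality of continuous variables will be checked graphically and through K-M and Shapiro-Wilk tests", and in the same sentence group differences are to be examined with "parametric tests (T-Tests, ANOVA) or non-parametric tests (Mann–Whitney U, Kruskal- Wallis". No cut-off or decision rule is written. The link between the check and the choice of test is implied by the sentence.
- **Significance level.** "The level of statistical significance will be 0.05".
- **Sample size.** It rests on a different quantity, a binary one: "a difference of 15 % in the frequency of patients that get at discharge a functional improvement greater than 10 points in Barthel Index".

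Under Study design and setting, "The data for both the intervention group and the control group will be obtained at four different times": the initial visit, discharge, and one and three months later. Table 1 marks SPPB, Barthel Index, MMSE, gait velocity and the strength measures at baseline and at all three later times. The Primary outcome section says "The primary outcome measure is the change in functional and cognitive status during the study period". It gives the SPPB a range of 0 to 12 and treats a one-point change as clinically relevant.

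**The concern.** There are two separate issues, both about choices that the text makes rather than details it leaves out.

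**Precision.** A change score subtracts the whole baseline value, which amounts to fixing the regression slope on baseline at 1. When baseline and follow-up are imperfectly correlated, that slope is too steep and adds baseline noise to the outcome. Estimating the slope instead removes the noise. The baseline values are already collected, so the loss is avoidable.

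**Effect measure.** SPPB is scored in whole points over a short range. Shapiro-Wilk responds to ties and coarse steps as well as to real departures from normality. At this group size it can reject for rounding alone and steer the outcome to a rank test. A rank test does not estimate a mean difference in points, yet the protocol's own yardstick for SPPB is one point. Whether the main test can be read against that yardstick would then be known only once the data are in.

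**Working it through.** **Inputs.** From the article: 161 per group before losses, significance level 0.05, SPPB range 0 to 12 with one point relevant. Not in the article, hence assumed: the baseline-to-follow-up correlation r, taken as 0.3 to 0.9; the SD of SPPB change, taken as 2 to 3 points; two-sided testing; equal variance s² at baseline and follow-up.

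**The plan's own figure.** The 161 concerns the Barthel responder proportion. It cannot be re-derived, because the control rate and power are not stated, but it is attainable: 29% versus 44% at 80% power, two-sided, gives 161. It is used below only as a realistic group size.

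**Step 1: variance of the two analyses.** Let B be baseline and Y follow-up. For any slope b,

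Var(Y − bB) = s²(1 − 2br + b²).

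- Change score, b = 1: 2s²(1 − r).
- Baseline-adjusted, b = r (the variance-minimising slope): s²(1 − r²).
- Ratio, adjusted to change: (1 − r²) / [2(1 − r)] = (1 + r)/2.

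The ratio is below 1 for every r below 1, so the change score is never the more precise of the two.

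**Step 2: size.** The third column is 161 × (1 + r)/2, rounded up. The last column takes the true difference for which the change score would have 80% power with 161 per group.

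| Assumed r | Variance ratio | Per-group n for the same precision as 161 on change scores | Power of the adjusted analysis |
|---|---|---|---|
| 0.3 | 0.65 | 105 | about 93.5% |
| 0.5 | 0.75 | 121 | about 90% |
| 0.7 | 0.85 | 137 | about 86% |
| 0.9 | 0.95 | 153 | about 82% |

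Confidence intervals shrink by the square root of the ratio: to 81%, 87%, 92% and 97% of the change-score width.

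**Step 3: how whole-point scores fare on Shapiro-Wilk.** Normally distributed changes were simulated, rounded to whole points, and tested at 0.05 with 157 to 185 patients in a group. The rounding is then the only departure from normality.

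| Assumed SD of change (points) | Rejection in a single group |
|---|---|
| 2 | 100% |
| 2.5 | 91–98% |
| 3 | 53–70% |

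If normality is required in both groups, the rank test is chosen more often still.

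**Step 4: does the two-stage choice damage type I error?** Null simulation, 161 per group, 5,000 runs for each distribution. The rule was a t-test if both groups pass Shapiro-Wilk, otherwise Mann-Whitney.

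| Data | Type I error |
|---|---|
| Normal | 0.0498 |
| Rounded integer change, SD 2 | 0.0502 |
| Exponential | 0.0498 |

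The nominal 0.05 is kept, so the harm lies in what is estimated and not in the error rate.

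**The case against.** The strongest reply is that nothing here is invalid. Change scores are unbiased under randomisation, and a two-group t-test or Mann-Whitney test on one difference per patient is a proper analysis. The gain from adjustment depends entirely on an r that the article does not give, and at r = 0.9 it is only 5% of the variance. The powered endpoint is a proportion, for which the article lists chi-square and Fisher tests, so the precision loss does not show the trial to be underpowered. Normality is also to be judged graphically, no mechanical rule is written, and means with confidence intervals are planned descriptively, so a mean change could still be shown beside a rank test. All of this stands. It limits the size of the point but does not remove it: the adjustment costs nothing, and the main test for SPPB is still left to the data.

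Three stronger readings are tempting, and the article supports none of them.

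- *Repeated visits are treated as independent.* A reader might infer this because four visits are planned, only generic tests are named, and "A Bonferroni post-hoc test will be used to evaluate statically significant" group and time differences. But no sentence pools visits as separate observations, one difference per patient is itself a within-patient contrast, and the ANOVA may well be a repeated-measures one.
- *Standard errors for time contrasts are wrong.* This follows only from the first reading and falls with it.
- *Results rest on completers only.* A difference needs a final value, but the article states no missing-data rule, and a condensed article may leave that to a full protocol or analysis plan that is not shown.

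**Conclusion.** The point holds as an avoidable loss of precision, together with a main test that the data would choose. It is not an error that invalidates the comparison.

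For the repeated continuous outcomes, adjusting for baseline cuts the variance to (1 + r)/2 of its change-score value: a saving of 35%, 25%, 15% or 5% at r = 0.3, 0.5, 0.7 or 0.9. This assumes equal variances at the two times, and r itself is an assumption. The result cannot be turned into a corrected sample size, because the 161 per group belongs to the Barthel responder proportion. Outcomes without a baseline value, such as mortality and new admissions, are outside the point.

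The normality check does not materially inflate type I error. Its cost is that SPPB would often be sent to a rank test because it is scored in whole points: nearly always at an assumed SD of 2 to 2.5, and in roughly half to two-thirds of single-group tests at SD 3. The main test would then not deliver a mean difference to compare with the one-point relevance the protocol states.

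**What to change.** For each repeated continuous outcome, replace the comparison of raw changes with a baseline-adjusted analysis, in one of two forms:

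- ANCOVA of the discharge value on group and baseline; or
- a linear mixed model for the values at discharge, one month and three months (T2 to T4), with baseline, visit, group and group-by-visit as fixed effects and correlation within patients allowed for.

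Report the adjusted group difference with its 95% CI at discharge (T2), the time point already used for the sample size. Remove the normality check as a gate for choosing the test. Keep Mann-Whitney on the change to discharge as a sensitivity analysis.

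The cost is a change of wording in the Statistics and sample size section. Every value needed is already scheduled in Table 1, so no extra data are required.
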